**Statistical analysis**

People will enter the cohort on 01/12/2020 (start date) and censored on the earliest date of outcome of interest (hospitalisation, ICU admission, or death) or end of the study period 11/04/2022 (end date). Individuals with the outcome of interest before the study start date will be excluded from the primary analysis.

Conditional logistic regression models will be used to report odds ratios and 95% confidence intervals between vaccinated and unvaccinated groups, adjusting for covariates as listed below. Subgroups of immunocompromising conditions will also be examined using the same methods described above, provided there is sufficient data for analysis.

We will conduct stratified analyses by calendar time to account for different SARS-CoV-2 variants circulating in the UK. We will split calendar time into the following intervals (ref 36 in main text):

- Alpha: 18 Dec 2020 – 17 May 2021
- Delta: 18 May 2021 – 19 Dec 2021
- Omicron BA.1: 20 Dec 2021 – 1 March 2022

*Covariates*

- Previous SARS-CoV-2 infection (ref 37 in main text).
- Socioeconomic status as measured by the Townsend score
- Ethnicity
- BMI (consider multiple imputation for missing values)
- Co-morbidities: 36 underlying clinical conditions identified using the QCOVID risk algorithm, where available in the dataset (ref 32 in main text). Co-morbidities will be grouped as below and included in the model by the following categories:
- Cardiovascular conditions (atrial fibrillation, heart failure, stroke, peripheral vascular disease, coronary heart disease, congenital heart disease)
- Diabetes (type 1 and type 2)
- Respiratory conditions (asthma, rare respiratory conditions (cystic fibrosis, bronchiectasis, or alveolitis), chronic obstructive pulmonary disease, pulmonary hypertension or pulmonary fibrosis)
- Cancer (lung or oral cancer, marrow transplant, radiotherapy)
- Neurological conditions (cerebral palsy, Parkinson’s disease, rare neurological conditions (motor neurone disease, multiple sclerosis, myasthenia, Huntington’s chorea), epilepsy, dementia, learning disability, severe mental illness)
- Other conditions (liver cirrhosis, osteoporotic fracture, rheumatoid arthritis or systemic lupus erythematosus, sickle cell disease, venous thromboembolism, solid organ transplant, renal failure (CKD3, CKD4, CKD5, with or without dialysis or transplant))
- Medications (prescriptions from general practitioner in previous six months for oral steroids, long acting β agonists or leukotrienes, immunosuppressants)
- Chemotherapy – (compare active chemotherapy during study period, previous chemotherapy in 6 months prior to study start date, and those not treated with chemotherapy from 6 months before the study start date)

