**Matching**

All cases who had the outcome will be matched with 10 controls who did not have the outcome on that date by matching on age, sex, calendar date and GP practice using incidence density sampling (ref 35 in main text). We will remove GP practice from the matching criteria if there is not a sufficient number of controls to match to each case in the blood cancer group.

We will undertake matching in the cohort of immunocompromised patients and the general population separately.

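### Care-home residence is neither matched on nor adjusted for, so the dose-specific odds ratios may be confounded by it, with a size and direction that the SAP does not allow one to fix

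*SAP*

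**What the plan says.** The Matching section pairs each case with 10 controls "by matching on age, sex, calendar date and GP practice using incidence density sampling". For blood cancer cases it then allows one of those factors to go: "We will remove GP practice from the matching criteria if there is not a sufficient number of controls to match to each case". Matching is done separately in the immunocompromised cohort and the general population.

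The Statistical analysis section specifies conditional logistic regression "adjusting for covariates as listed below". The list is explicit:

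- previous SARS-CoV-2 infection
- "Socioeconomic status as measured by the Townsend score"
- ethnicity
- BMI
- "36 underlying clinical conditions identified using the QCOVID risk algorithm, where available in the dataset", entered as grouped categories
- medications, namely "prescriptions from general practitioner in previous six months for oral steroids" and certain other drug classes
- chemotherapy

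The neurological group contains "epilepsy, dementia, learning disability, severe mental illness" along with cerebral palsy, Parkinson's disease and rare neurological conditions. No item in the SAP refers to a care home or to any other residential setting.

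**The concern.** The SAP itself fixes the adjustment set of the primary model item by item, so this is not a detail that one would expect to find in the protocol instead. A resident of a care home and a person of the same age and sex living at home, registered with the same practice, can form a case-control pair, and nothing in the model tells them apart except recorded illness, drugs and deprivation. Residence could plausibly relate both to when a person was vaccinated and to the risk of a severe outcome. If both links survive the matching and the listed covariates, residence confounds the odds ratios.

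The one-dose and two-dose estimates are the most exposed, because differences in vaccination date matter most while coverage is still rising. The cohort opens on 01/12/2020 and the Alpha stratum runs from 18 Dec 2020 to 17 May 2021, so that phase lies inside the study. For the second objective, the two cohorts are matched and modelled separately. Any residence bias cancels in their comparison only if it is of similar size in both.

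**Working it through.** **Step 1. Is residence controlled directly?** No. It is absent from the four matching factors and from every item of the covariate list.

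**Step 2. Is it controlled indirectly?** Partly.

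- GP practice: matching on it does not separate residents from others in the same practice, and it may be removed.
- Townsend score: listed as a measure of socioeconomic status.
- Dementia and learning disability: the closest clinical markers, but they enter through one neurological category with conditions of quite different relevance. A single coefficient for that mixture cannot stand in for residence.
- Other listed conditions, such as stroke and osteoporotic fracture, carry some further information.

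**Step 3. How large could the bias be?** The SAP gives no share of residents, no risk ratio and no vaccine coverage, so there is no figure to reproduce. Every input below is an assumption.

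For a binary factor left out of the model, the observed odds ratio is approximately the true odds ratio × B, with

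B = [1 + p1(g − 1)] / [1 + p0(g − 1)].

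Here p1 and p0 are the shares of residents among vaccinated and unvaccinated people in the risk set, and g is the residents' risk ratio for the outcome. If residents make up a share q of the risk set, with coverage c1 in residents and c0 in others on the index date, then

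p1 = q·c1 / [q·c1 + (1 − q)·c0] and p0 = q(1 − c1) / [q(1 − c1) + (1 − q)(1 − c0)].

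Worked case with q = 0.06, g = 5, c1 = 0.60, c0 = 0.30:

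- p1 = 0.036 / (0.036 + 0.282) = 0.113
- p0 = 0.024 / (0.024 + 0.658) = 0.035
- B = (1 + 4 × 0.1132) / (1 + 4 × 0.0352) = 1.453 / 1.141 = 1.27

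A true odds ratio of 0.40 would appear as 0.40 × 1.27 = 0.51, so apparent effectiveness falls from 60% to 49%.

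The same formula gives:

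| q | g | c1 v c0 | B | 0.40 appears as |
|---|---|---|---|---|
| 3% | 3 | 50% v 30% | 1.05 | 0.42 |
| 6% | 5 | 60% v 30% | 1.27 | 0.51 |
| 12% | 5 | 60% v 30% | 1.44 | 0.58 |
| 6% | 5 | 95% v 90% | 1.11 | 0.45 |

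**Step 4. Is the direction fixed?** No. All four rows assume that residents are both better vaccinated and at higher risk, so they can only give B above 1. Setting p1, p0 and g directly shows the wider picture:

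| Situation | p1 / p0 | g | B |
|---|---|---|---|
| Strong imbalance, higher risk | 0.10/0.02 to 0.30/0.05 | 2 to 5 | 1.08 to 1.83 |
| Little imbalance left | 0.10/0.08 | 2 to 5 | 1.02 to 1.06 |
| Fewer residents among the vaccinated | 0.05/0.10 | 2 to 5 | 0.95 to 0.86 |
| Few residents in an early-dose window | 0.02/0.05 | 2 to 5 | 0.97 to 0.90 |
| Residents less often have the outcome | 0.10/0.02 to 0.30/0.05 | 0.7 | 0.98 to 0.92 |

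The fourth row matters because the Exposure definition section splits each dose by time since vaccination. If residents were vaccinated first, they would later have left the 14-27 day window after dose 1 for the 42+ day window or for dose 2. At those index dates the early window could hold few residents. The last row could apply to hospitalisation, if residents are admitted less readily than others.

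**The case against.** The strongest objection is that the causal premise is not in the document. The SAP states no roll-out order, no resident share and no excess risk. A reader might infer from the omission that early-dose odds ratios in older people are pulled toward no effect. The SAP does not support that as a flat statement. It holds only if residents were vaccinated earlier and keep a higher risk after matching and adjustment. Step 4 shows that other plausible conditions make the bias negligible or reverse it.

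Three further points stand:

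- The factor of 1.05 to 1.44 is one-sided by construction. Its risk ratios of 3 and 5 are not residual to the planned adjustment for dementia, stroke, renal failure, BMI, deprivation and the rest. Residual ratios would probably be smaller.
- A reader might also infer that the distortion is greater in the older general population and therefore carries into the second objective in a known direction. The SAP gives neither the age mix nor the residence mix of either cohort, so this cannot be said.
- Nothing shows that the dataset carries a residence flag. Even the clinical conditions are limited to those available.

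These points narrow the claim but leave the gap in place. The proxies remain partial, and uncertainty about size and direction is a reason to measure residence where that can be done.

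**Conclusion.** The point holds in conditional form. It is certain that residence is not matched on, not a listed covariate, and only partly covered by proxies. Confounding of the dose-specific odds ratios follows if residents differ from matched people at home both in vaccination timing and in residual risk.

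If they were vaccinated earlier and were at higher risk, the odds ratio for death is biased upward. The illustrative factor is 1.05 to 1.44 on assumed resident shares of 3% to 12%, risk ratios of 3 to 5 and the coverages shown. It could be larger with stronger imbalance, and it is near 1 if matching and covariates leave little. For hospitalisation, and in some time-since-dose windows, the bias may be small or in the other direction. The effect on the comparison in the second objective depends on the residence mix of the two cohorts, which the SAP does not give.

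**What to change.** In the covariate list, add care-home (residential or nursing home) residence at the index date as its own indicator, where it can be derived from the dataset. Controls should be classified at the index date of their case. Keep it separate from the neurological group. Add a sensitivity analysis that repeats the death and hospitalisation models excluding residents, in both cohorts. If the information cannot be derived, state residual confounding by residence as a limitation, without claiming a direction for every outcome and window.

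The cost is one covariate and one repeat of two models. The matching and the design do not change. The downside is some misclassification of the flag, which would leave part of the confounding in the adjusted model. The analysis without residents would share that weakness, since unflagged residents would stay in.

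### The pooled immunocompromised analysis neither matches on nor separately adjusts for type of immunocompromising condition, so the vaccine odds ratios may carry residual confounding

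*SAP*

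**What the plan says.** Under Matching, the SAP draws ten controls per case "by matching on age, sex, calendar date and GP practice using incidence density sampling", and GP practice may be dropped if controls run short. It adds: "We will undertake matching in the cohort of immunocompromised patients and the general population separately". The same section mentions dropping practice "if there is not a sufficient number of controls to match to each case in the blood cancer group", without saying whether that group is a matched cohort of its own.

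Under Statistical analysis, "Conditional logistic regression models will be used to report odds ratios and 95% confidence intervals between vaccinated and unvaccinated groups", adjusted for the listed covariates. For co-morbidities, "Co-morbidities will be grouped as below and included in the model by the following categories". The cancer category reads "Cancer (lung or oral cancer, marrow transplant, radiotherapy" and does not include blood cancer. The category for other conditions puts solid organ transplant and rheumatoid arthritis or lupus together with cirrhosis, osteoporotic fracture, sickle cell disease, venous thromboembolism and renal failure. Further covariates cover GP prescriptions in the past six months (oral steroids and immunosuppressants among them) and a three-level chemotherapy variable.

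On subgroups: "Subgroups of immunocompromising conditions will also be examined using the same methods described above", if data suffice. So the cohort holds more than one condition. The SAP does not list which conditions define it.

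**The concern.** Matching the immunocompromised cohort apart from the general population holds constant the fact of being immunocompromised, but not the kind. A case with one condition can be set against controls with quite different conditions. If those conditions differ both in the risk of severe COVID-19 and in how many patients are vaccinated, or how early, part of the difference in vaccination between cases and controls reflects condition rather than vaccine.

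The first objective is the comparison within the immunocompromised group, so the pooled odds ratio is a main result. The characteristic that defines the cohort is not controlled there in its own right. Condition-specific subgroups would hold it constant, but they depend on sufficient data and do not change the pooled estimate.

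**Working it through.** **Coverage of condition type in the text**

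- *Matching factors:* age, sex, date, practice. Condition type is absent.
- *Blood cancer:* in no co-morbidity category. A patient with blood cancer and no lung or oral cancer, marrow transplant or radiotherapy is coded zero on the cancer term.
- *Solid organ transplant, rheumatoid arthritis or lupus:* one shared term. A transplant case and an arthritis control carry the same value, so the term adjusts nothing between them.
- *Marrow transplant:* shares the cancer term with lung and oral cancer.
- *Proxies:* the medication item counts GP prescriptions only. The chemotherapy item is defined by the study period and study start, not by the index date. Both relate to treatment, and neither identifies the condition.

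**Possible size**

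The SAP gives no prevalences, uptake or rate ratios, so there is no figure of its own to reproduce. All inputs here are assumptions. Take a high-risk condition in 20% of the cohort, an outcome rate 5 times that of the rest, and a true odds ratio of 0.50. No covariate adjustment is applied.

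Formula: crude OR = (cases vaccinated / cases unvaccinated) ÷ (controls vaccinated / controls unvaccinated).

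*High-risk patients better vaccinated (unvaccinated 5% v 10%)*
- Controls unvaccinated: 0.2 × 0.05 + 0.8 × 0.10 = 0.09; vaccinated 0.91.
- Cases unvaccinated (relative units): 0.2 × 5 × 0.05 + 0.8 × 0.10 = 0.13.
- Cases vaccinated: 0.50 × (0.2 × 5 × 0.95 + 0.8 × 0.90) = 0.835.
- Crude OR: (0.835/0.13) ÷ (0.91/0.09) = 0.635, an effectiveness of 36% instead of 50%.

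*High-risk patients less vaccinated (unvaccinated 10% v 5%)*
- Controls: 0.06 unvaccinated, 0.94 vaccinated.
- Cases unvaccinated: 0.2 × 5 × 0.10 + 0.8 × 0.05 = 0.14.
- Cases vaccinated: 0.50 × (0.2 × 5 × 0.90 + 0.8 × 0.95) = 0.83.
- Crude OR: (0.83/0.14) ÷ (0.94/0.06) = 0.378, an effectiveness of 62%.

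*Equal uptake (unvaccinated 10% in both)*
- Controls 0.10/0.90; cases 0.18/0.81; crude OR = 4.5 ÷ 9 = 0.50. No bias.

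**Cross-check with a bias factor for an omitted binary confounder**

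BF = [p1(R − 1) + 1] / [p0(R − 1) + 1], where R is the condition's risk ratio and p1 and p0 are its prevalence in vaccinated and unvaccinated people. For a true OR of 0.50:

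| R | p1 | p0 | BF | Observed OR |
|---|---|---|---|---|
| 1.5 | 0.25 | 0.20 | 1.125/1.10 = 1.023 | 0.51 |
| 4 | 0.40 | 0.20 | 2.2/1.6 = 1.375 | 0.69 |
| 4 | 0.20 | 0.40 | 1.6/2.2 = 0.727 | 0.36 |

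BF is 1 when R = 1 or p1 = p0.

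**Bias left inside the pooled category for other conditions**

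Assume risk ratios of 4 for transplant and 1.3 for the rest. Among the vaccinated, transplant is 20% of the cohort and the rest of the category 20%; among the unvaccinated, 10% and 30%.

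- Mean risk, vaccinated: (0.2 × 4 + 0.2 × 1.3)/0.4 = 2.65.
- Mean risk, unvaccinated: (0.1 × 4 + 0.3 × 1.3)/0.4 = 1.975.
- Ratio: 2.65/1.975 = 1.34, or 0.75 with the shares reversed.

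The grouped term can thus leave bias behind even after adjustment for it.

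**The case against.** Several counter-arguments carry weight.

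- *Confounding is not shown.* It needs condition type to be related both to vaccination and to outcome, given the matching factors and covariates. The SAP has figures for neither. A reader might infer that condition type does confound the odds ratios; the document supports only that it can. This stands.
- *There is partial adjustment.* Immunosuppressants, oral steroids, chemotherapy and the grouped terms capture some of the difference, and the two-stratum calculation gives them no credit. This stands as to size; it does not close the gap.
- *Subgroups.* A reader might infer that subgroup analyses would split the pooled matched sets and strand cases without same-condition controls. The SAP does not say so. The methods to be reused include the matching, so re-matching within each subgroup is a fair reading. What remains is a request to say it.
- *Blood cancer may be its own matched group.* If so, an indicator would be constant within each of its sets and its absence harmless there. The text is ambiguous, and the point would still apply to the pooled cohort.
- *Cohort membership.* The SAP does not show that rheumatoid arthritis, sickle cell disease or renal failure define the cohort, so there is no ground here for ungrouping CKD stages, for example.
- *Parsimony.* Vaccination status already has 1 + 4 + 7 + 8 = 20 indicative levels, and indicators for rare conditions may be sparse. This is a reason to combine the rarest, not to omit condition type.

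**Conclusion.** The point holds for the pooled immunocompromised analysis. As written, neither matching nor model separates the conditions that define the cohort, and blood cancer, the one condition named in the objectives, is in no covariate group. Residual confounding is possible in either direction and cannot be sized from the SAP. Under the two-stratum assumptions above a true odds ratio of 0.50 would appear as 0.38 to 0.64; the bias-factor assumptions give 0.36 to 0.69 at their extremes and 0.51 in their mildest unequal case. These are unadjusted illustrations, not predictions. The point does not extend to analyses restricted to one condition with controls drawn from that same condition. It is a worthwhile, inexpensive improvement rather than a flaw that invalidates the plan.

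**What to change.** - In the pooled within-cohort model, enter each cohort-defining immunocompromising condition, including blood cancer, as its own indicator at the index date, and take it out of the grouped co-morbidity terms. Combine the rarest conditions if they are sparse. The other co-morbidity groups can stay as they are.
- State in the Matching section that controls for the blood cancer group, and for every other condition subgroup, are drawn from that condition's own risk set. No indicator for that condition is needed in those analyses.

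Cost: SAP wording, a few more model terms and a small loss of precision. The conditions must already be identified to define the cohort. If per-subgroup matching is already intended, the second change is only a sentence; otherwise the sampling is repeated for each subgroup.

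### Chemotherapy is coded by study calendar dates, not by the matched index date, so it uses post-index records and misses recent treatment

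*SAP*

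**What the plan says.** Chemotherapy is one of the covariates listed in the SAP under Statistical analysis. It has three levels. Two are set out as "compare active chemotherapy during study period, previous chemotherapy in 6 months prior to study start date". The third takes in everyone else, described as "those not treated with chemotherapy from 6 months before the study start date". The first two are tied to the study period and the study start. The third runs forward from six months before the start and has no stated end. None refers to the date on which the case had the outcome.

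The Matching section makes that date central. Each case is to be "matched with 10 controls who did not have the outcome on that date by matching on age, sex, calendar date and GP practice", by incidence density sampling, so the case's outcome date is the index date for the whole matched set.

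Follow-up starts on 01/12/2020, and people are "censored on the earliest date of outcome of interest (hospitalisation, ICU admission, or death) or end of the study period 11/04/2022 (end date". The conditional logistic models then estimate vaccine odds ratios "adjusting for covariates as listed below", and chemotherapy is on that list. The neighbouring medications item uses a look-back that is not tied to study start: "prescriptions from general practitioner in previous six months for oral steroids" and other drugs.

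**The concern.** In an incidence-density design, case and controls are compared as they stood on the index date, so a covariate should be known by then and measured over the same look-back in every member of the set. The chemotherapy item does neither. Three consequences follow from the wording:

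- A person can be coded active because of treatment given months after the index date.
- A case who dies cannot accrue later chemotherapy, while a living control can. A hospitalised case may have later chemotherapy changed by the admission itself.
- The previous level recedes in time as the study runs, so treatment given shortly before a late index date is not separated from treatment at any other time in the study.

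At stake are the contrast between the chemotherapy levels and how well chemotherapy is controlled as a confounder.

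**Working it through.** The SAP gives no figure on this point, so there is none to reproduce.

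**Inputs from the SAP.** Study start 01/12/2020; end 11/04/2022; variant-period dates from Statistical analysis (18 Dec 2020, 17 May 2021, 19 Dec 2021, 1 Mar 2022). **Assumptions, not in the SAP:** the rate λ at which people start chemotherapy, the share p₀ already on it at study start, and no true chemotherapy effect unless stated.

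**1. Share of the active window after the index date.** Start to end is T = 496 days. With t days from start to index, the share is (496 − t)/496.

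| Index date | Days before | Days after | Share after |
|---|---|---|---|
| 18 Dec 2020 | 17 | 479 | 97% |
| 17 May 2021 | 167 | 329 | 66% |
| 19 Dec 2021 | 383 | 113 | 23% |
| 1 Mar 2022 | 455 | 41 | 8% |

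**2. Age of the previous level.** It covers 1 June to 1 December 2020. Seen from 1 March 2022, that is about 21 to 15 months earlier.

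**3. Fatal cases.** Records stop at death. Let a control be followed to study end. The probability of being coded active is

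P(w) = p₀ + (1 − p₀)(1 − exp(−λw/365.25)),

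with w = t for the case and w = 496 for the control. The artefactual odds ratio is the ratio of the two odds.

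For a death on 15 January 2021 (t = 45) and λ = 10% per year:

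- p₀ = 0: case 1.2%, control 12.7%; odds 0.0124/0.1455, OR about 0.09.
- p₀ = 10%: case 0.1 + 0.9 × 0.0122 = 11.1%; control 0.1 + 0.9 × 0.127 = 21.4%; odds 0.125/0.273, OR about 0.46.
- p₀ = 20%: OR about 0.61.

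For deaths on 1 July 2021 (t = 212) and 15 January 2022 (t = 410), the ORs are 0.41 and 0.82 with p₀ = 0, and 0.65 and 0.89 with p₀ = 10%. The start rate matters little: at t = 45 and p₀ = 0, the OR runs from about 0.09 at 5% per year to 0.07 at 30%. The share already on treatment matters a great deal.

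**4. Simulation of the coding choices.** 4,000 sets of one case and ten controls; index day uniform from day 17 to day 455; start rates of 10% and 30% per year; nobody on chemotherapy at study start; true vaccine OR 0.4; vaccination probability 60% in those who had started chemotherapy by the index date and 80% otherwise. There was one run per setting, so small differences are noise. The ranges are across the two start rates.

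| Chemotherapy coding | Estimate, true OR 1.0 | Estimate, true OR 2.0 |
|---|---|---|
| Up to the index date, all | 1.05–1.06 | 1.89–2.12 |
| Whole study period, all | 0.95–0.96 | 1.55–1.57 |
| Cases cut at outcome, controls to study end | 0.43–0.51 | 0.81–0.94 |

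The second row applies to hospitalised survivors if their records run to study end; the run did not model an effect of the outcome on later treatment. The third row applies to deaths. The vaccine OR came out at 0.37–0.42 under all three codings, with no difference distinguishable from noise.

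**The case against.** The best reply is that the wording is loose shorthand. With incidence density sampling named in Matching and a six-month look-back for other medications, the analysts may intend chemotherapy status at the index date. That is possible for the active level, though the text says otherwise. It cannot rescue the previous level, which is explicitly tied to study start.

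Three further objections stand and limit the point.

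- **Unequal windows.** A reader might infer that controls always get a longer window than cases, so that chemotherapy will look protective or its effect will be reversed. The SAP does not support this in general. The censoring rule ends follow-up for the outcome; it does not say that chemotherapy records stop at hospitalisation. The shorter window is forced only for deaths. With a common full-period window, the simulation showed dilution, not reversal.
- **Size.** The 0.09 assumes nobody is on chemotherapy at study start, an early death, and a control followed for all 496 days. Anyone already on treatment is active in case and control alike, which pulls the OR towards 1. Controls can also die or become cases, which shortens their window.
- **Purpose.** The odds ratios to be reported compare vaccinated with unvaccinated people, and no objective names a chemotherapy effect. The word compare in a covariate list may only introduce the levels.

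**Conclusion.** The definition is wrong as written for this design. It admits post-index records for every index date before the last day of the study, and for late index dates its previous level does not describe recent treatment. Both follow from the stated dates and need no assumption.

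For fatal cases, the chemotherapy odds ratio is biased downwards, most for early deaths. The values of 0.09 and 0.46 for a death on 15 January 2021 are illustrations that rest on the assumed start rate and baseline share. For hospitalised survivors whose records run to study end, the windows are equal, but the covariate is still misclassified, can be affected by the outcome, and dilutes a true effect (2.0 to about 1.55–1.57 in the simulation).

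A reader might also infer that the vaccine odds ratios are materially biased. That is not shown: the size of any such bias cannot be derived from the SAP. The established damage is to the chemotherapy contrast and to the quality of confounding control.

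**What to change.** Define all three levels relative to each matched set's index date, identically for the case and its controls. For example: current, a chemotherapy record in a fixed short window before the index date; recent, an earlier record within the six months before the index date; none, no record in those six months. State that no record dated after the index date is used. Within each set the windows are then equal, so the artefact from unequal windows disappears by construction. The cost is a change of SAP wording and a recode of dated chemotherapy records; no new data are needed.
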